## Discussion

School feeding interventions are implemented in nearly every country in the world, with the potential to support the education, health and nutrition of school children from low-income households [23]. To date, there is little evidence on the potential for agriculture and community development. This paper described the design and baseline results for a randomised evaluation of school meals interventions linked to smallholder agriculture. As far as we are aware, it is the first to examine explicitly from a holistic perspective the simultaneous impact of a national school meals programme on micronutrient status, alongside outcomes in nutrition, education and agriculture domains. The evaluation builds on a trial design taking place in Mali that includes an extensive analysis of the programme theory for the intervention. As the intervention is complex, the scope of this evaluation is also very broad and includes measurement of a range of outcome indicators across multiple traditional disciplines. Designing and implementing such an evaluation is in itself a complex undertaking, involving a multi-disciplinary research team working in close collaboration with programme- and policy-level stakeholders. The survey also required a range of different expertise in the enumeration teams in order to collect data including anthropometry, haemoglobin levels, and educational tests, alongside expenditure, income and other socio-economic-related modules. The use of the survey tools required to capture the data was inevitably fairly time-intensive. Extensive analysis of the rich baseline data is currently underway.

A number of important considerations can be drawn from the baseline data analysis. Firstly, the tests of balance showed evidence of small differences across the treatment arms for several variables across education, nutrition, agriculture and other socio-economic domains. The randomisation of treatment across the arms of the cluster-randomised trial is aimed at minimising the systematic differences in the outcomes between the intervention groups. In practice, differences between the intervention groups can arise due to sampling error in moderate sample sizes. When estimating programme impact it is important to control for these differences where they exist.

In addition, approximately 19 % of children in the target age group (5–15 years) received some form of free school meals at baseline. Similar findings were reported in a similar study in Mali in 2013 by Masset and Gelli [13] where, because of information flow constraints, the original list of schools used in the randomisation included schools with school feeding. This finding has important implications in terms of the evaluation design, considerably reducing sample sizes available for comparisons after the follow-up survey. The small sample sizes between the HGSF+ and HGSF++ comparisons are a particular concern, and power calculations using the baseline data suggest folding these two arms into one, adding micronutrient sprinkles to the HGSF+ intervention.

Significant differences were found in the means of a number of outcome and control variables across the intervention groups. It appears, therefore, that at baseline the random allocation process did not achieve statistically comparable treatment groups. In particular, important differences across groups include marketed surplus, livestock income, per capita food consumption and intake, school attendance, anthropometric status in the 2–5 and 5–15 years age groups. Differences in outcome and control variables across groups will be controlled when estimating treatment effects. More in-depth analyses of the very rich baseline dataset, examining the associations between key outcomes and variables along the complex agriculture-nutrition are also underway.

## Conclusions

Assessing the simultaneous impact of ‘home-grown’ school feeding on micronutrient status, health, education and agriculture is a complex undertaking, involving coordination across policy, programme and research stakeholders. This study is the first to examine the effects of alternative implementation modalities of school meals on nutrition, health education and agriculture in Ghana. The findings of this evaluation will provide important evidence to support policymakers in the scale-up of the national programme.

## Appendix 1

### Power calculations

#### School attendance

We used the rural sample of the GDHS data of 2008 to estimate attendance rates of children in the age group 6 to 14 and we found rates of 79 % for boys and 81 % for girls. The chart below plots values of power for increasing number of clusters assuming a project impact of 5 percentage points on attendance rates in primary school. A sample of just 60 clusters and collecting data on 40 children is sufficient to detect such an impact with 80 % statistical power (Fig. 4).

#### Cognitive tests

We obtained data on outcomes of cognitive tests from a sample of rural children tested in 2003 using Raven’s matrices. The average score on the test was 15.3 out of 36 questions with a SD of 5.9 and an intracluster correlation coefficient (ICC) of 0.14. The chart below plots that minimum detectable difference against the number of clusters. We assumed a number of 40 children per cluster considering 20 households interviewed in each cluster and an average of 2.3 children in the relevant age group per each household with children (Fig. 5).

The table below summarises the standardised detectable differences and corresponding absolute values of the tests for different study designs (Table 7).

**Table 7 Tab7:** Raven’s tests: standardised detectable differences and equivalent levels for different designs

	Children aged 6 to 14 (in SDs)	Equivalent level
30 clusters	0.43	2.5
60 clusters	0.30	1.8
120 clusters	0.21	1.2

*SD* standard deviation

#### Anaemia

Data for power calculations were obtained from the 2008 GDHS. We calculated means, SDs, and ICCs for rural children aged 6 months to 5 years and rural mothers aged 15–49 years. See the tables below for the level of haemoglobin and prevalence rates of any anaemia (including severe, moderate and mild) (Table 8).

**Table 8 Tab8:** Haemoglobin levels and anemia prevalence rates (rural mothers and under-5 s)

	Mean	SD	ICC	Observations.
Children (haemo)	9.22	1.73	0.126	1473
Children (prevalence)	0.854	0.35	0.045	1473
Mothers (haemo)	11.9	1.78	0.080	2681
Mothers (prevalence)	0.619	0.49	0.052	2681

*ICC* intracluster correlation coefficient, *SD* standard deviation

The chart below plots the minimum detectable difference in terms of SDs from the mean for children (ICC = 0.13) and mothers (ICC = 0.08). In both cases it is assumed that the size of the sample in each cluster is 20. This is consistent with 20 household interviews per community and considering that several children may end up not being tested. In any case, only a marginal gain can be obtained by expanding the sample beyond 20 as power is mainly driven by the number of clusters (Fig. 6).

The table below reports the standardised detectable differences and their equivalent level values for 3 different designs: 30 clusters, 60 clusters and 120 clusters. In each case 50 % of the sample is allocated to the project group. Differences between groups of mothers can be estimated more precisely because the ICC is lower for mothers though the sample variance is slightly larger (Table 9).

**Table 9 Tab9:** Haemoglobin: standardised detectable differences and equivalent levels for different designs

	Children (in SDs)	Equivalent level	Mothers (in SDs)	Equivalent level
30 clusters	0.44	0.76	0.38	0.65
60 clusters	0.31	0.56	0.26	0.46
120 clusters	0.21	0.36	0.18	0.32

*SD* standard deviation

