### Sample sizes

For the impact evaluation, power calculations and resource availability suggested the adoption of a sample of 25 households from the communities in the areas of the 58 schools receiving the intervention and of 20 households in the communities of the 58 control schools.

Households were randomly selected from household listings in the catchment areas of the selected schools for the survey interviews. The household listings were stratified into farmer/non-farmer households, based on agriculture classification data from the national census. Farmer households were sampled in both areas in the following way: 10 out of the 25 households in the 60 intervention communities were farmer households and 5 out of the 20 households in the 60 control communities were farmer households. Non-farmer households with children in the 5–15 years age group were randomly selected from the household listings. This distribution of the sample between farmer and non-farmer households and between project control groups allows the construction of comparable samples (see Table 2).

**Table 2 Tab2:** Sample sizes

	Districts	Schools	Households with children in the 5–15 years age group	Farmer HH	Children^a^
Control	58	58	870	290	2375
GSFP	29	29	435	290	1383
HGSF+	29	29	435	290	1383
(HGSF++)	(14)	(14)	(210)	(140)	(668)
Total	58	116	1740	900	5142

^a^the number of children is an estimate based on an average of 2.28 children per family in families with children and 1.35 children per family in farmer households

*GSFP* Ghana School Feeding Programme, *HGSF* ‘home-grown’ school feeding, *HH* households

In each household, all children aged between 5 and 15 years were asked education outcome-related questions (enrolment, attendance, drop-out) and were tested in literacy, maths, forward and backward digit span and Raven-like matrices. Anthropometry and haemoglobin level measurements were administered to children aged 5–15 years. Anthropometry indicators were also be measured for children aged 2–5 years. As each school is assigned a caterer by the GSFP programme, the sample also included 58 caterers who were interviewed using a semi-structured questionnaire.

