In each household, all children aged between 5 and 15 years were asked education-related questions (enrolment, attendance, drop-out) and were tested in literacy, maths, forward and backward digit span and Raven’s matrices. Anthropometry measurements were undertaken for children aged 2–15 years. Tests and measurements were made at the household level because not all the children in the targeted schools resided in the selected localities where the schools were situated. Height measurements were taken with Leicester Height Measures and weights were measured using Tanita Electronic Scales WB-100A/WB-110A Remote Display Version scales, which allow height measurements of up to 2 m 10 cm to the nearest 1 mm. The height and weight measures were assembled and placed on a level surface. In the absence of a level ground in the household, a suitable place was identified for the measurement in the community. A sub-set of children aged 5–15 years were randomly selected for haemoglobin and parasitology measurements. Haemoglobin levels were collected using HemoCue Hb 201+ analyser, with standard controls reagents (Hemotrols) used to verify appropriate device function on a daily basis.

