Haemoglobin levels (g/dL)	714	11.3 [1.34]	422	11.3 [1.35]	169	11.3 [1.36]	32	11.4 [1.47]	91	11.3 [1.21]	0.9088	0.8764	0.8469
Total maize production volumes (kg)	2626	787 [1751]	1163	864 [2034]	722	807 [1596]	375	590 [1248]	366	702 [1478]	0.0439	0.0376	0.2646
Total rice production volumes (kg)	2626	141 [652]	1163	149 [700]	722	148 [645]	375	137 [678]	366	111 [449]	0.6003	0.4551	0.5297
Total maize sale volumes (kg)	2626	393 [1196]	1163	432 [1261]	722	446 [1337]	375	270 [880]	366	292 [907]	0.1381	0.0057	0.7435
Total rice sale volumes (kg)	2626	84 [484]	1163	94 [583]	722	87 [413]	375	70 [397]	366	61 [327]	0.3509	0.2895	0.7286
Other variables													
Age (for 15 years and younger)	8407	7.5 [4.2]	3153	5.8 [9.0]	1918	6.2 [9.5]	942	6.2 [9.3]	917	6.1 [9.9]	0.057	0.847	0.8071
Is a girl? (for 15 years and younger)	8407	0.48 [0.5]	3799	0.48 [0.50]	2318	0.49 [0.50]	1167	0.47 [0.50]	1123	0.51 [0.5]	0.4933	0.9377	0.0989
Birth order (for all children)	8533	2.9 [2.0]	3791	2.9 [2.1]	2397	3.0 [2.0]	1189	3.0 [2.0]	1156	2.9 [1.9]	0.8275	0.021	0.2204
Is enrolled in school? (for 5–15 years)	6178	0.92 [0.27]	2755	0.91 [0.29]	1737	0.92 [0.26]	852	0.94 [0.01]	834	0.91 [0.29]	0.0375	0.9395	0.0065
Receives free school meals?	6280	0.19 [0.39]	2809	0.17 [0.38]	1768	0.23 [0.42]	860	0.13 [0.34]	843	0.24 [0.43]	0.0001	0.0055	<0.001
Distance to nearest school	6343	0.47 [3.24]	2765	0.45 [3.14]	1808	0.58 [4.34]	891	0.21 [0.85]	879	0.59 [2.29]	0.597	0.0992	<0.001
Time to school	6333	21.4 [45.6]	2778	19.6 [31.3]	1796	18.8 [32.5]	888	17.6 [22.7]	871	35.9 [95.1]	0.007	<0.001	<0.001
Total education expenditure	5635	23923 [35642]	2410	19250 [30878]	1640	27089 [37899]	789	25732 [37096]	796	29752 [40791]	<0.001	0.6249	0.0403
Mother’s education level (5–15 years)	5096	5.9 [9.4]	2290	5.7 [9.1]	1437	6.1 [9.6]	690	6.1 [9.4]	679	6.0 [9.8]	0.1946	0.8518	0.7608
Education level of head of household	2626	1.4 [2.6]	1163	1.4 [2.7]	1463	1.3 [2.5]	375	1.6 [2.7]	366	1.3 [2.2]	0.9393	0.2147	0.1344
Household size	2626	5.7 [2.4]	1163	5.7 [2.4]	722	5.8 [2.4]	375	5.7 [2.3]	366	5.6 [2.3]	0.8747	0.1774	0.5572
Per-capita expenditure quintile	2625	3.1 [1.4]	1162	3.2 [1.4]	722	2.9 [1.4]	375	3.3 [1.4]	366	3.1 [1.4]	0.1763	0.0008	0.2199
Household expenditure on food	2626	3473 [2187]	1163	3483 [2213]	722	3370 [2254]	375	3502 [1846]	366	3608 [2289]	0.815	0.1041	0.4874
Household expenditure on health	2626	93.5 [112]	1163	97.7 [116]	722	88.7 [107]	375	93.3 [108]	366	90.0 [112]	0.0894	0.595	0.6768

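### The haemoglobin detectable differences in Table 9 assume 20 people measured per community; baseline yielded about 6 (about 2 in HGSF+), so in SD units the table overstates the trial's sensitivity

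*Protocol article*

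**What the plan says.** Table 1 lists haemoglobin in 5–15 year olds among the impact indicators, and the anaemia sub-study is built around fortification.

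Appendix 1 (Anaemia) takes its planning inputs from "rural children aged 6 months to 5 years and rural mothers aged 15–49 years". Table 8 gives an SD of 1.73 and ICC of 0.126 for the children, and 1.78 and 0.080 for the mothers. The appendix fixes the cluster size ("In both cases it is assumed that the size of the sample in each cluster is 20") and the allocation ("In each case 50 % of the sample is allocated to the project group"). For children, Table 9 then states 0.44, 0.31 and 0.21 SD (0.76, 0.56 and 0.36 g/dL) at 30, 60 and 120 clusters.

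Under Sample sizes the article says "Anthropometry and haemoglobin level measurements were administered to children aged" 5 to 15. Under Data collection it says that a sub-set of that age group "were randomly selected for haemoglobin and parasitology measurements". Table 6 gives the yield: 714 children, of whom 422 were control, 169 GSFP, 32 HGSF+ and 91 HGSF++.

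Methods of analysis names two estimators: a difference-in-difference written in arm means, and an ANCOVA with the child's own baseline value as a regressor. The Discussion calls the small HGSF+ and HGSF++ samples a concern and suggests merging the two arms. It does not mention haemoglobin there.

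**The concern.** The article was written with the baseline counts in hand, yet Table 9 still rests on 20 measured per community, in age groups other than the one to be analysed. Twenty in each of 116 communities would be 2,320 people; 714 is 31% of that.

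Micronutrient status is part of the study's headline aim. If endline haemoglobin shows no difference, readers will judge that result against Table 9. If the trial cannot detect what the table says, a null result will look more informative than it is. The analysis set is a second issue: an ANCOVA that conditions on each child's own baseline discards every child first measured at endline.

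**Working it through.** **Inputs.** ICC 0.126 (Table 8; 0.13 in the text) and m = 20 (Appendix 1). There are 58 control, 29 GSFP, 15 HGSF+ and 14 HGSF++ communities (29 less 14 gives 15). Counts and the baseline SD of 1.34 g/dL are from Table 6. Two-sided 5% is assumed. The article states 80% power for attendance ("is sufficient to detect such an impact with 80 % statistical power"), and I assume it for haemoglobin too.

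**Formula.** MDD = (t₀.₉₇₅ + t₀.₈₀) × √(V₁ + V₂), where V = [1 + (m − 1) × ICC] / (J × m) for an arm with J communities and m children in each, and df = J₁ + J₂ − 2.

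**Step 1: reproduce Table 9.** With m = 20 and ICC 0.13, the design effect is 1 + 19 × 0.13 = 3.47.
- 60 clusters: V = 3.47/600 = 0.00578 per arm; 2.850 × √0.01157 = 0.306.
- 30 and 120 clusters by the same route: 0.442 and 0.215.

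The stated values are 0.31, 0.44 and 0.21, so the SD column is reproduced to within 0.005 at its declared inputs.

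**Step 2: numbers measured per community.** Control 422/58 = 7.3; GSFP 169/29 = 5.8; HGSF+ 32/15 = 2.1; HGSF++ 91/14 = 6.5; overall 714/116 = 6.2.

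**Step 3: detectable differences at the baseline yield, ICC 0.126.**
- School feeding v control (292 v 422 children): V = 0.00517 + 0.00424; 2.826 × √0.00941 = 0.27 SD.
- GSFP v HGSF (169 v 123): V = 0.00952 + 0.01145; 2.851 × √0.02097 = 0.41 SD.
- HGSF+ v HGSF++ (32 v 91): V = 0.03571 + 0.01860; 2.907 × √0.05431 = 0.68 SD.

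| Contrast | Stated SD (Table 9, nearest design) | m = 20, actual clusters | Baseline yield | Range, ICC 0.05–0.20 |
|---|---|---|---|---|
| School feeding v control | 0.21 | 0.22 | 0.27 | 0.24–0.30 |
| GSFP v HGSF | 0.31 | 0.31 | 0.41 | 0.37–0.45 |
| HGSF+ v HGSF++ | 0.44 | 0.45 | 0.68 | 0.63–0.72 |

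Power at the stated 0.21, 0.31 and 0.44 SD (noncentral t) is about 57%, 55% and 44% at ICC 0.13. At ICC 0.126 the values are 57.4%, 55.7% and 44.5%.

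**Step 4: the same in g/dL at SD 1.34, ICC 0.126.** 0.274 × 1.34 = 0.37; 0.413 × 1.34 = 0.55; 0.678 × 1.34 = 0.91. Table 9 states 0.36, 0.56 and 0.76. Had 20 per community been reached, the figures would be 0.29, 0.41 and 0.60. Precision was therefore lost in all three contrasts, but for the first two the smaller SD in 5–15 year olds offsets the loss relative to the printed table.

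**Side point.** Two equivalent levels in Table 9 do not follow from the SD columns: 0.31 × 1.73 = 0.54 (stated 0.56) and, for mothers, 0.38 × 1.78 = 0.68 (stated 0.65).

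**The case against.** Several stronger readings are tempting, and the article does not support them.

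- *The sensitivity is overstated for every contrast.* This is true in SD units. In g/dL the two larger contrasts come out almost where Table 9 puts them, as step 4 shows.
- *Both estimators are capped at 714 children.* Only ANCOVA with the child's own baseline, and a within-child difference-in-difference, are capped. The printed difference-in-difference formula is in arm means and needs no linkage between rounds. The article also rests causal identification on arm means at endline.
- *The power figures describe the trial as it will be analysed.* They are conditional. The article does not state how many children will have haemoglobin measured at endline, nor how the 714 were spread over communities. The ICC comes from under-5s, school feeding v control is treated as unpaired although schools were matched within districts, and no gain from baseline adjustment is credited because no correlation is given.
- *The sub-set was drawn at different rates by arm.* Against the free-school-meals denominators in Table 6, the measured shares are 422/2809 = 15%, 169/1768 = 10%, 32/860 = 4% and 91/843 = 11%. Table 6 counts children measured, not children selected, so refusal or field failure could give the same pattern.
- *Sample sizes and Data collection contradict each other.* The first does not clearly say that every child had haemoglobin measured, so the two can be read together.

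It is also fair to say that the planning populations are openly declared, and that the Discussion already flags the contrast with the largest figure. That passage does not name haemoglobin, however, and merging the two arms would leave GSFP v HGSF at 169 v 123 children and about 0.41 SD.

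**Conclusion.** The point holds as a planning calculation that the baseline yield has overtaken. The SD column of Table 9 is correct at its own inputs, but those inputs (20 per community, under-5s and mothers) are not this trial's. If the endline yield resembles baseline and is evenly spread, the detectable differences are about 0.27, 0.41 and 0.68 SD rather than 0.21, 0.31 and 0.44, and all three exceed the stated values throughout ICC 0.05–0.20. On the g/dL scale, at the baseline SD and ICC 0.126, the shortfall against the printed table is material only for HGSF+ v HGSF++ (0.91 against 0.76). An uneven spread over communities would make the figures worse; a larger endline sample or useful covariates would make them better. The 714 ceiling, before attrition, applies to analyses that need each child's own baseline and to no others.

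**What to change.** 1. Restate Table 9 by contrast for children aged 5–15, using the trial's own SD (1.34), the numbers measured per community and a range of ICCs, in SD units and in g/dL. Say that the figures depend on the endline yield.
2. For haemoglobin, make the main analysis the endline comparison of all children measured at endline. Use cluster-robust standard errors and adjust for covariates available for all of them, such as age, sex and, for school feeding v control, the district pair. Keep individual-baseline ANCOVA as a supporting analysis.
3. Allocate whatever endline haemoglobin tests are planned evenly per community across arms.

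Substituting a community-mean baseline with a missing-value indicator is not a good way round the ceiling. With about two children per community in HGSF+ the mean is very noisy, and missingness would track arm.

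The cost is less favourable published figures in SD units and a changed haemoglobin analysis set. Even allocation of the planned tests needs no extra tests; measuring more children than planned would be a real additional cost and is a separate decision.

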#### Child nutrition

We used data from the GDHS 2008 to estimate mean and SD of height-for-age *z*-scores of rural children and we found these to be −1.03 and 1.57 respectively. The ICC is 0.08. The chart below plots the standardised minimum detectable difference against the number of clusters assuming a sample of 30 children measured in each community (Fig. 7).

The table below summarises the values of the standardised and equivalent absolute values of the detectable differences (Table 10).

**Table 10 Tab10:** Height-for-age *z*-scores (HAZ): standardised detectable differences and equivalent levels for different designs

	Children under 5 years (in SDs)	Equivalent level
30 clusters	0.35	0.55
60 clusters	0.25	0.39
120 clusters	0.17	0.27

*SD* standard deviation

#### Farm income

We used data from GLSS4 of 1998/1999 to estimate average farm income of rural households (1200 cedis) and relative SD (1400 cedis). We found an extremely high ICC. Income is the most difficult outcome to estimate with sufficient precision. The chart below plots the standardised minimum detectable difference against the number of clusters assuming 20 farmers interviewed in each community. Since the SD is roughly similar to the mean the vertical axis can be interpreted as a percentage difference (Fig. 8).

The table below summarises the standardised differences and the corresponding percentage changes in income that can be estimated with different study designs (Table 11).

**Table 11 Tab11:** Farm income: standardised detectable differences and equivalent levels for different designs

	Farm incomes (in SDs)	Percentage difference
30 clusters	0.6	0.69
60 clusters	0.4	0.46
120 clusters	0.3	0.35

*SD* standard deviation

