### Agriculture and community development

The intervention will have an impact on a small number of farmers in the intervention communities. Other persons in the community may benefit either directly or indirectly via an increase in incomeThe programme will have an impact on a small number of caterers involved in the school feeding service provision

In addition to examining the potential effects in the different domains, the evaluation will also assess the pathways through which these effects are mediated.

Table 1 includes a list of the main outcome indicators of the study. The data collection section below describes how data will be collected using different survey instruments. All the main study outcomes, including school enrolment, attendance and test scores, will be obtained through the household- and child-level interviews.

**Table 1 Tab1:** Primary indicators for the evaluation

Type	Domain	Indicator
Impact	Agriculture	Household income, production, sales
	Education	Child enrolment, attendance, completion, maths and literacy scores (5–15 year olds)
	Cognition	Raven’s test and forward/backward digit span scores (5–15 year olds)
	Physical health/Nutrition	Anthropometry (height-for-age, BMI-for-age, 2–15 year olds), haemoglobin levels (5–15 year olds)
Outcome	Food consumption	Nutrient adequacy and dietary diversity score (individual and household)
Output	Meal service	Quality of school meals, portion sizes, frequency and timeliness

For the pathways analysis, in addition to the outcome indicators in Table 1 we will also observe the programme impact on intermediate indicators, particularly for those outcomes that are more difficult to observe directly. In the case of farmer income, we will look at several intermediate outcomes such as input use (labour, land, seeds and fertiliser), investments (farm capital such as tools and machinery), and market access (marketed surplus, prices and markets). In terms of other intermediate indicators in the nutrition and health pathway, we will observe the effect of the programme on knowledge and practices of caterers and school management members, and on the quantity, quality, and timeliness of the preparation and delivery of the school meals.

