The GSFP selected 58 districts in which the programme will be implemented. In each of these districts, two candidate schools were selected and each school was randomly assigned to the treatment or to the control. A protocol was designed in order to ensure that the schools were comparable based on data from the Education Management Information system (EMIS) and that contamination between the two schools in each district will be minimised. This will allow comparison of outcomes of the intervention against the control group at the school level in 58 districts. The 58 schools assigned to the intervention were then randomly assigned to regular GSFP and HGSF+. In this way the randomisation of the HGSF+ intervention occurs at the district level. The number of 58 schools is based on power calculations (see Appendix 1) determined with the objective of achieving statistical validity and representativeness for the main outcomes of interest.

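### The farm-income detectable differences assume 20 farmers per community, but the sample has 10 and 5, so Table 11 is modestly too favourable

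*Protocol article*

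**What the plan says.** **Power calculation.** Appendix 1, Farm income, takes a mean of 1200 cedis and an SD of 1400 cedis from a 1998/1999 survey. It calls the ICC extremely high without giving a value and computes detectable differences "assuming 20 farmers interviewed in each community". Table 11 reports 0.6, 0.4 and 0.3 SD at 30, 60 and 120 clusters, shown as 69%, 46% and 35% of mean income.

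**Sample.** Under Sample sizes, the intervention side is described as follows: "10 out of the 25 households in the 60 intervention communities were farmer households". The control side has fewer per community: "5 out of the 20 households in the 60 control communities were farmer households". Table 2 agrees on the number per community: 290 farmer households in 58 control schools (5 each), 290 in 29 GSFP schools and 290 in 29 HGSF+ schools (10 each). The text says 60 communities per side where Table 2 has 58; 58 is used below.

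**Comparisons.** For school feeding v control, "This will allow comparison of outcomes of the intervention against the control group at the school level in 58 districts". For the home-grown component, "In this way the randomisation of the HGSF+ intervention occurs at the district level", which gives 29 v 29.

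**Status of the outcome.** The abstract lists smallholder farmer income among the primary outcomes, and Table 1 has household income as an impact indicator. The number of schools is said to be "determined with the objective of achieving statistical validity and representativeness for the main outcomes of interest". The agriculture hypothesis reads: "The intervention will have an impact on a small number of farmers in the intervention communities".

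**The concern.** No community in the design has 20 sampled farmer households, so Table 11 describes a different sample. Fewer farmers per cluster means a larger detectable difference. A reader who takes 35% or 46% from Table 11 will think the trial somewhat more sensitive than it is.

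This matters because the article presents the evaluation as the first to examine the agriculture pathway. HGSF+ v GSFP is the randomised test of the farmer-linkage component. If its power is overstated, a non-significant income result is more easily taken as evidence that farmers gained nothing.

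The second issue is the kind of effect. Table 11 concerns the mean over all sampled farmers, while the hypothesis expects direct impact on few of them. Gains confined to a few are diluted in that mean, and the appendix does not discuss this.

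**Working it through.** **Inputs.** Mean 1200 and SD 1400 cedis (Appendix 1); 20 farmers per community (Appendix 1) against 10 and 5 (Sample sizes, Table 2); 58 v 58 and 29 v 29 clusters. Assumed: 80% power (stated only for attendance), two-sided 5% (not stated), equal allocation (stated only for haemoglobin). The within-district pairing of schools is ignored.

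**Formula.** MDE = (t₀.₉₇₅ + t₀.₈₀) × √[(ρ + (1−ρ)/m₁)/k₁ + (ρ + (1−ρ)/m₂)/k₂], with k clusters and m farmers per cluster in each arm, ρ the ICC, and k₁ + k₂ − 2 degrees of freedom.

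**Check against the appendix's other tables** (30/60/120 clusters):
- Raven's (m = 40, ρ = 0.14): 0.426/0.296/0.207; stated 0.43/0.30/0.21.
- Child haemoglobin (m = 20, ρ = 0.13): 0.44/0.31/0.215; stated 0.44/0.31/0.21.
- Height-for-age (m = 30, ρ = 0.08): 0.353/0.245/0.172; stated 0.35/0.25/0.17.

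The formula and the assumed power and significance level therefore match the appendix.

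**ICC implied by Table 11.** It can only be back-solved. Converting the percentages to SDs (× 1200/1400) with m = 20 gives 0.275, 0.250 and 0.304, so 0.25–0.30 is used. The SDs are rounded to one decimal, and taking each row singly at ±0.05 SD widens the range to about 0.19–0.44.

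**School feeding v control, 58 v 58 (multiplier 2.826).**
- ρ = 0.25, 20/20: √[(0.2875 + 0.2875)/58] = 0.0996; MDE 0.281 SD; × 1400/1200 = 32.8%.
- ρ = 0.25, 10/5: √[(0.325 + 0.400)/58] = 0.1118; MDE 0.316 SD = 36.9%.
- ρ = 0.30, 20/20: √[(0.335 + 0.335)/58] = 0.1075; MDE 0.304 SD = 35.4%.
- ρ = 0.30, 10/5: √[(0.370 + 0.440)/58] = 0.1182; MDE 0.334 SD = 39.0%.

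**HGSF+ v GSFP, 29 v 29 (multiplier 2.851).**
- ρ = 0.25, 20/20: √[0.575/29] = 0.1408; MDE 0.401 SD = 46.8%.
- ρ = 0.25, 10/10: √[0.650/29] = 0.1497; MDE 0.427 SD = 49.8%.
- ρ = 0.30, 20/20: √[0.670/29] = 0.1520; MDE 0.433 SD = 50.6%.
- ρ = 0.30, 10/10: √[0.740/29] = 0.1597; MDE 0.455 SD = 53.1%.

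**Effect of the farmer count alone.** At the same ICC and clusters, the MDE rises by 10–12% in relative terms for school feeding v control (√(0.810/0.670) = 1.10; √(0.725/0.575) = 1.12). For HGSF+ v GSFP it rises by 5–6% (√(0.740/0.670) = 1.05; √(0.650/0.575) = 1.06).

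**Wider ICC range.** From 0.19 to 0.44, the MDEs with the actual farmer numbers are about 34–44% and 45–61%.

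**Power at Table 11's own differences** (ρ = 0.29, normal approximation, Φ(δ/SE − 1.96)):
- School feeding v control at 0.3 SD: SE 0.1059 with 20/20 gives 81%; SE 0.1169 with 10/5 gives 73%.
- HGSF+ v GSFP at 0.4 SD: SE 0.1498 with 20/20 gives 76%; SE 0.1578 with 10/10 gives 72%.

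**The case against.** **The effect is small and rests on an unstated ICC.** This stands. Clusters drive precision here, and the higher the ICC, the less the farmer count matters: at 0.44 the MDE increases fall to about 6% and 3%. The mismatch remains, and the figures are wrong in one direction.

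**The whole gap to Table 11 is not due to farmers.** For HGSF+ v GSFP, a reader might set 50–53% beside the printed 46% and blame the farmer count for all of it. Part comes from one-decimal rounding and from 58 rather than 60 clusters. The farmer count adds about 3 percentage points.

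**Farm income might be analysed in all households.** Table 1 speaks of household income, the household questionnaire covers farm income, and Table 6 reports crop volumes for all 2626 households. With 25/20 households per community the same formula gives 32.6–35.2% for school feeding v control, about Table 11's value. This is a fair caveat, but the appendix refers to farmers and the article does not say that all households will be used. The planned ANCOVA could also lower the MDE by an unknown amount.

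**The article is candid.** It calls income the hardest outcome to estimate precisely, attributes the household numbers to resources as well as power, and already plans to examine intermediate outcomes such as marketed surplus and prices. That covers much of the interpretive worry but does not correct the assumed sample.

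**Two stronger readings are not supported.** A reader might infer that the programme cannot produce an average change this large. The documents give neither an expected income effect nor the share of farmers who benefit, and the hypothesis adds that others in the community may gain, directly or indirectly. Required gains per supplying farmer would rest on an invented share. A reader might also infer that differences below the MDE could not be excluded. An MDE at 80% power is not a confidence limit. The 95% half-width is about 70% of it (1.981/2.826; 2.003/2.851), or roughly 26–27% and 35–37% of mean income, so a null result would still be informative.

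**Conclusion.** The point holds in limited form. Table 11 assumes 20 farmers per community where the design has 10 and 5, so the stated detectable differences are modestly too favourable for a primary outcome. At an ICC of 0.25–0.30 the design detects about 37–39% of mean income for school feeding v control and 50–53% for HGSF+ v GSFP. At the table's own standardised differences both comparisons fall below 80% power (73% and 72% at ICC 0.29), though the second would do so even with 20 farmers.

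These values rest on a back-solved ICC, assumed 80% power and two-sided 5%, the 1998/1999 mean and SD, and an analysis restricted to farmer households. That average changes of this size look hard to reconcile with impact on few farmers is a matter of judgement, which the article leaves unaddressed; it is not a demonstrated impossibility.

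**What to change.** - Restate Table 11 for 58 v 58 clusters with 10/5 farmers and 29 v 29 clusters with 10/10, using the SD and ICC from the 2013 baseline, and print the ICC, power and significance level.
- If farm income will be analysed in all sampled households, say so and use 25/20 per community for school feeding v control.
- Beside the farm-income outcome, give the average difference detectable with 80% power for each comparison. State that a non-significant result will be read from its confidence interval and not as absence of effect on farmers.

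The cost is a recalculation and a few sentences. On the present inputs one stated figure becomes slightly less favourable. No extra interviews are needed.
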